# 10.0 TRIAL MANAGEMENT

We recognize participants in the SAEP group may experience an increase in their symptoms due to physical exertion. Despite the current usual care recommendation of rest until symptoms resolve, there is no evidence in humans suggesting exercise after 72 hours of rest is harmful. Nonetheless, symptoms will be monitored throughout the exercise session by a trained kinesiologist using a prepared script to allow the supervising researcher to determine symptom exacerbation (change of >3 points on symptom checklist, adopted by previous AE studies for individuals with PCS)^39^. Should symptoms significantly increase during an AE session, it will be terminated immediately. Furthermore, if a participant in the AE group experiences a significant increase in symptoms over the course of two consecutive sessions, their participation will be terminated. To further ensure participant safety, the AE sessions will take place in a training facility adjacent to the MacIntosh Clinic; immediate access to a physician will be available if required.

# 11.0 STUDY ENROLMENT & WITHDRAWEL

Potential participants will be informed of the study by a member of the research team. During the initial phase of the appointment, when the potential participants is completing the initial concussion forms, a member of the research team will assist them and answer any questions they might have. At this time, the member of the research team will explain that they may be eligible for the study. If a member of the research team is unavailable, potential participants will be informed of the study by their diagnosing physician at their initial medical assessment post-injury, and will be given an information flyer and confirmation that they can be contacted by phone by a member of the research team.

To ensure that all potential participants and their parents/guardians are fully aware of what they are consenting to, a member of the research team will brief them in person about the study’s purpose, methods, and possible risks prior to having them sign the informed consent documents. At this point, potential participants and their parents/guardians will have the opportunity to ask any questions that they may have with respect to the study before consenting to participate. The member of the research team will take this opportunity to remind the potential participants and their parents/guardians that their choice to participate is entirely voluntary, and that they have the option to withdraw themselves from the study at any point without any negative repercussions. The primary informed consent document for this study clearly outlines the purpose, procedures and potential risks of participation in this study. The parents/guardians of potential participants who are under the age of 16 will be required to sign this form on their child’s behalf, in addition to signing a parental consent form. Additionally, children under the age of 16 will be required to sign a child assent form. This will ensure that all aspects of the study are clearly articulated to both the potential participants and their parents/guardians, and that everyone involved is fully aware of what they are consenting to.

In the event of a participant’s withdrawal from the study, their data will be safely discarded with no consequences to the participant. The patient will continue to be able to have access to customary care at the David L. MacIntosh Sport Medicine Clinic. Participants are permitted to withdraw from the study at any point during data collection

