Participants in the SAEP may also experience symptom exacerbation later in the day following the exercise intervention, even after they have left the testing facility. In order to minimize this risk, participants will be kept at the facility for an additional 10 minutes following the completion of the entire exercise session (including the 5 minute cool-down period) in order for the supervising researcher to monitor their symptoms and ensure that they their HR and BP have returned to pre-exercise levels. Additionally, participants in this group will be provided with the contact information for the David L. Macintosh Clinic, where a sports-medicine physician will be available on-call at all times should the participant require urgent care after they have left the facility. Finally, there may be minor and temporary discomfort associated with the blood-drawing procedure. This may include soreness or bruising of the skin in area of the blood-draw. This should resolve within a few days after the blood draw. Risks of experiencing infection or irritation of the skin surrounding the site of the blood acquisition will be minimal due to the training of the phlebotomist on site. If a sample cannot be acquired due to difficulties in locating a vein, or if a vein collapses, we will ask the participant if they are comfortable with one additional attempt on the opposite arm. If they are not comfortable with this, or if we are unable to acquire a sample on the other arm, we will terminate the blood acquisition portion of the assessment for the participant. Psychological/Emotional Risks Participants may become upset or frustrated if they lack progress in their perceived recovery time. In order to mitigate the potential mental health-associated risks that may arise due to participation in this study, participants’ will be given priority scheduling to be seen by a physician at the Macintosh Clinic, who will monitor them for mental health-related symptoms and refer them for psychiatric care if necessary. In addition to including the contact information for the Macintosh Clinic, the informed consent documents have been updated to provide participants with the contact information for local mental health treatment centres in the area that they may access should they require additional psychiatric resources.

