## Measures

9.6.1 Clinical Assessment: At the first medical visit post-injury, participants will be evaluated by one of three treating physicians at the MacIntosh Clinic. The clinical assessment includes Sport Concussion Assessment Tool-5 (SCAT5), which includes information about the mechanism of injury, medical history, symptoms (PCSS), cognitive abilities, physical examination, and additional injuries/co-morbidities. Clinical management and corresponding follow-up evaluations will be at the discretion of the caring physician. Date of medical clearance will be obtained from medical records.

9.6.2 Physician and Research Assistant Blinding: To minimize bias, physicians will be blinded to the randomization of participants to either SAEP or usual care groups. Furthermore, all participants will be specifically instructed not to inform their treating physician of their group assignment at any point throughout the duration of the study. In addition, the randomization procedure will be overseen by a member of the research team who is not involved with the consent process.

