# 14.0 DESCRIPTION OF STATISTICAL METHODS

## 14.1 Analysis of Primary Endpoints

We will statistically evaluate time to medical clearance between the standard of care and AE intervention groups by Cox regression (or proportional hazards regression). This approach allows one to control for the effect of several variables (i.e., sex/gender, age, initial PCSS), while evaluating a single outcome measure. Furthermore, we have the ability account for censor subjects who are removed from the study due to exercise-induced symptom exacerbation or attrition.

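### Section 11.0 discards the data of anyone who withdraws, while Section 14.1 relies on censoring for attrition; for formal withdrawers both rules cannot be followed

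*Protocol*

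**What the plan says.** Section 11.0 of the protocol (study enrolment and withdrawal) states that after a withdrawal "their data will be safely discarded with no consequences to the participant". The sentence covers both arms and all data. It makes no exception for data already collected and does not depend on a deletion request. The same paragraph adds: "Participants are permitted to withdraw from the study at any point during data collection". Participation lasts 90 days (Section 2.0), so a withdrawal may come before or after medical clearance.

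Section 14.1 sets Cox regression for time to medical clearance and gives as one of its advantages that "we have the ability account for censor subjects who are removed from the study due to exercise-induced symptom exacerbation or attrition".

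Two other places bear on the point. Section 9.6.1 gives the source of the endpoint: "Date of medical clearance will be obtained from medical records". Section 7.0 lists a psychological risk: "Participants may become upset or frustrated if they lack progress in their perceived recovery time".

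**The concern.** Voluntary withdrawal is one form of attrition. To censor a participant in a Cox model, the analyst needs the randomised group, the covariates and the time at risk up to exit. A discarded record supplies none of these. The sentence in Section 11.0 is a positive instruction, so a statistical analysis plan could not repair it afterwards: data that have been destroyed cannot be censored.

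At stake is the set of randomised participants behind the primary comparison. Deleting people after allocation is harmless to the comparison only if withdrawal is unrelated to recovery or acts alike in both arms. Neither is assured. Participants know their allocation (Section 9.6.2 tells them to keep it from their physician), so withdrawal could differ by arm. It could also depend on how recovery is going. The point concerns formal withdrawal in either arm. Exercise-arm participants removed for symptom exacerbation have separate rules and are not covered here.

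**Working it through.** **1. The two rules side by side, for a participant who withdraws on day d without having been cleared.**

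| | Section 11.0 | Section 14.1 |
|---|---|---|
| Record kept | none | up to day d |
| Time at risk in the Cox model | 0 | d days |
| Status | absent | censored at d |

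For a participant who withdraws after clearance, Section 11.0 deletes an observed event that needs no censoring at all.

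**2. Inputs from the documents.** Mean time to clearance 43 days, SD 20, target difference 7 days, 53 per group (Section 13.0); 90 days of participation (Section 2.0). No figure for withdrawal is given, so everything below that needs one is an assumption. The plan states no figure for this point that could be reproduced.

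**3. Precision.** Discarding 10%, 20% or 30% of 53 leaves 53 × 0.9 ≈ 48, 53 × 0.8 ≈ 42 or 53 × 0.7 ≈ 37 per group. For a two-sided 5% comparison of means with difference 7 and SD 20 (7/20 = 0.35), power falls from 44% to 40%, 36% or 33%. The low starting value is a separate matter.

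**4. Who is lost depends on when they leave.** Assume gamma clearance times (mean 43, SD 20), with about 20% withdrawing by day 90.

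| Timing of withdrawal | Mean of discarded (days) | Mean of kept (days) |
|---|---|---|
| Only before clearance | 50.8 | 41.1 |
| Constant rate to day 90 | 43.0 | 43.0 |
| Only after clearance | 35.5 | 44.8 |

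**5. Effect on the hazard ratio.** Cox model, exercise versus usual care, large-sample simulation, no true effect, day-90 cut-off, about 10% withdrawing in usual care and 30% in the exercise arm. A ratio above 1 means faster clearance in the exercise arm.

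| Timing of withdrawal | Censoring | Discarding |
|---|---|---|
| Only before clearance | 1.00 | 1.11 |
| Constant rate to day 90 | 1.00 | 1.00 |
| Only after clearance | 1.00 | 0.90 |

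With equal withdrawal in the two arms, discarding also gives 1.00.

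**6. One-arm illustration in days.** The gamma with mean 43 and SD 20 has shape (43/20)² = 4.6225 and scale 20²/43 = 9.30. Its slower half averages 58.48 days and its faster half 27.52. Let a proportion p withdraw, with probabilities w_S in the slower half and w_F in the faster half. Then

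retained mean = [0.5(1 − w_S) × 58.48 + 0.5(1 − w_F) × 27.52] / (1 − p).

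- Slower half three times as likely to withdraw (w_S = 1.5p, w_F = 0.5p). For p = 0.10: (0.5 × 0.85 × 58.48 + 0.5 × 0.95 × 27.52)/0.90 = 42.1. For p = 0.15 and 0.20: 41.6 and 41.1. The falls are 0.9, 1.4 and 1.9 days.
- All withdrawals from the slower half (w_S = 2p, w_F = 0). For p = 0.10, 0.15 and 0.20: 41.3, 40.3 and 39.1. The falls are 1.7, 2.7 and 3.9 days.

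If this happens in one arm only, the artefact is 0.9 to 3.9 days, that is 0.9/7 ≈ 12% to 3.9/7 ≈ 55% of the target difference. In a Cox model with no true effect, the same one-arm scenarios give hazard ratios after discarding of 1.04–1.10 (three times as likely) and 1.09–1.20 (all from the slower half), against 0.98–1.03 with censoring. With the same pattern in both arms, discarding gives 0.99–1.01.

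**The case against.** A reader might infer that the rule removes slow recoverers and so shortens apparent recovery. The documents do not support that. They give no rate, timing or reasons for withdrawal. They allow it up to day 90, well past the mean clearance time of 43 days, and late withdrawal would remove fast recoverers instead. The passage on frustration in Section 7.0 describes a psychological risk and its mitigation and does not mention withdrawal. The 0.9 to 3.9 day range builds in the assumption that slow recoverers leave more often, and only in one arm. It also compares means, whereas the planned analysis is a Cox model. All of this stands, and the range is only an illustration.

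A second objection also stands: attrition is wider than formal withdrawal. Participants who miss visits or are lost without asking to withdraw are untouched by Section 11.0 and can still be censored. Section 14.1 is therefore unworkable only for formal withdrawers.

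Three further inferences go beyond the text:
- That the clearance date is usually recoverable. Withdrawers keep access to the clinic, but nothing says that they attend or permit use of their records.
- That adverse-event information is deleted. The protocol does not say whether safety records count as the participant's data.
- That the consent form needs changing. It is not available here, and discarding may match what participants were promised.

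None of this removes the contradiction for formal withdrawers.

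**Conclusion.** The point holds for participants who formally withdraw. The discard rule in Section 11.0 and the censoring in Section 14.1 cannot both be applied to them. Obeying the discard rule takes randomised participants, and time at risk or events already observed, out of the primary analysis.

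The loss of information follows from the text alone. Bias does not: with no true effect, it needs withdrawal to be related to recovery and to differ by arm, and its direction is unknown. Under the assumed 10% versus 30% withdrawal, the null hazard ratio after discarding ranges from 0.90 to 1.11 according to timing. Censoring stays at 1.00 there because withdrawal in those scenarios is independent of clearance time; where the slower half withdraws more in one arm it stays close, at 0.98–1.03. These sizes rest on the gamma shape and the assumed withdrawal rates, which the documents neither give nor exclude.

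**What to change.** Replace the sentence in Section 11.0 so that:
- data collected up to withdrawal are kept and analysed in the randomised group, unless the participant asks for deletion;
- participants who withdraw are asked for permission to take the clearance date from clinic records;
- without that permission, a participant not yet cleared is censored at the withdrawal date, and Section 14.1 says so.

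Report the number of withdrawals, and of any deletions on request, by arm and by timing relative to clearance. Check whether the present consent wording allows data to be kept, and amend it for future participants if it does not.

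The cost is a small protocol amendment, possibly a consent amendment, and ethics notification, with no added visits or participants. It should be done before any withdrawer's data are destroyed, because that cannot be reversed.

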# 12.0 ADVERSE EVENT (AE) REPORTING

An AE may jeopardize the patient or participant and may require medical or surgical intervention. Examples of such medical events include allergic bronchospasm requiring intensive treatment in an emergency room or at home or convulsions that do not result in inpatient hospitalization. All AEs will be assessed by a MacIntosh Clinic physician using a protocol defined grading system.

**Mild** – Events require minimal or no treatment and do not interfere with the participant’s daily activities.

**Moderate** – Events result in a low level of inconvenience or concern with the therapeutic measures. Moderate events may cause some interference with functioning.

**Severe** – Events interrupt a participant’s usual daily activity and may require systemic drug therapy or other treatment. Severe events are usually potentially life-threatening or incapacitating.

# 13.0 SAMPLE SIZE

Sample size was determined from a power analysis incorporating published data by our group on days to medical clearance in high school patients evaluated at the MacIntosh Clinic (mean time to clearance = 43 days, SD = 20 days).^79^. Hence, to reduce time to medical clearance to 36 days (delta = 7), at a significance level of 0.05 and a at a moderate effect level (0.7), would require 53 participants per group.

# 14.0 DESCRIPTION OF STATISTICAL METHODS

## 14.1 Analysis of Primary Endpoints

We will statistically evaluate time to medical clearance between the standard of care and AE intervention groups by Cox regression (or proportional hazards regression). This approach allows one to control for the effect of several variables (i.e., sex/gender, age, initial PCSS), while evaluating a single outcome measure. Furthermore, we have the ability account for censor subjects who are removed from the study due to exercise-induced symptom exacerbation or attrition.

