# 7.0 POTENTIAL BENEFITS AND RISKS

Physical Risks During the study, participants in the Structured Aerobic Exercise Protocol (SAEP) group may experience an increase in their symptoms due to physical exertion. Should symptoms increase during a session, the session will be terminated immediately. If a participant in the exercise group experiences an increase in their symptoms over the course of two consecutive sessions, then their participation in the SAEP intervention will be terminated. While these participants will be removed from the larger group analysis, careful evaluation of this potential subset will be conducted. In addition, these participants will remain in the study and they will complete assessments on Days 7, 14, 21, 28, and 90 post-injury. In order to ensure the safety of all participants, there will be an on-call physician at all times available at the David L. Macintosh Sports Medicine Clinic, which is located directly next to the lab space in which the exercise sessions will take place.

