## 9.2 Intervention

**(1) Usual care (UCEP) group:** Participants allocated to the UCEP group were advised to follow the instructions, prescriptions, and recommendations given to them by the sport medicine physician. Aligned with consensus guidelines of a brief period of physical and cognitive rest, the physician advised participants to increase their activity levels gradually with minimal head movement (predominantly involving a stationary bike) and progressively increase levels of exertion while remaining under the threshold of symptom exacerbation.^78^ Subsequently, exercise included a progression of head movements, visual and cognitive burdens, sport-specific activities, and heavy resistance, in that order, all below the symptom exacerbation threshold. For more details on the UCEP, please see the **Appendix**. Any diagnosed concomitant neck injuries underwent concurrent rehabilitation. Completion of asymptomatic low-risk simulations of target activities was required prior to medical clearance to return to those activities.

**(2) Structured Aerobic Exercise Protocol (SAEP) group:** These individuals will begin to exercise at Day 3 post-injury. Participants will be asked to complete a total of eight exercise sessions over the course of 11 days, with one day of rest after two consecutive sessions. The participants will have their symptoms recorded before and after exercise, and monitored throughout each session. Symptoms will only be recorded during exercise if exacerbated, in which case the session will be terminated. If this occurs, patient will resume the same stage in the protocol at the subsequent session. If the patient’s symptoms become exacerbated for two consecutive sessions, they will be removed from the study and continue with clinic for patient follow-up. Should the participant achieve asymptomatic status at any point, they will continue with the exercise protocol until completion, while simultaneously being guided through the RTP guidelines.

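### Excluding or censoring exercise-arm participants who exacerbate breaks the randomised comparison and, if they tend to clear later, biases time to clearance in favour of exercise

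*Protocol*

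**What the plan says.** The primary analysis is in section 14.1: "We will statistically evaluate time to medical clearance between the standard of care and AE intervention groups by Cox regression", adjusted for variables such as sex, age and initial PCSS. The section adds that this method has the ability to "account for censor subjects who are removed from the study due to exercise-induced symptom exacerbation or attrition".

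Section 7.0 treats participants whose symptoms rise in two consecutive exercise sessions differently: "While these participants will be removed from the larger group analysis, careful evaluation of this potential subset will be conducted". It then says that "these participants will remain in the study and they will complete assessments on Days 7, 14, 21, 28, and 90 post-injury".

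Section 9.2 says of the same people that "they will be removed from the study and continue with clinic for patient follow-up". Section 10.0 ends participation "if a participant in the AE group experiences a significant increase in symptoms over the course of two consecutive sessions", without saying whether that means the exercise sessions or the study.

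No such rule is written for usual care, although section 9.2 has those participants raise their exertion gradually below a symptom threshold. The same usual-care text makes symptom-free completion of simulated activities a condition of clearance.

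On where the endpoint comes from, section 9.6.1 says: "Date of medical clearance will be obtained from medical records".

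**The concern.** Randomisation takes place at Day 3. Whether someone exacerbates in two consecutive exercise sessions is learned only afterwards, and only in the arm that receives the sessions. Excluding or censoring on that event therefore selects on a response to the assigned treatment in one arm, while comparable people in usual care stay in the analysis.

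Cox regression needs censoring to be unrelated to the remaining time to clearance, given the covariates. A person whose symptoms flare on exertion is plausibly someone who will clear late, because clearance is tied to symptom-free activity. The exercise arm would then lose some of its slower recoverers. At stake is a primary endpoint: an ineffective programme, or one that slows recovery in a subgroup, could appear to speed recovery.

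The loss is also avoidable, since clearance dates are in the medical record and sections 7.0 and 9.2 both foresee continued follow-up of some kind.

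**Working it through.** **Step 1. The passages side by side**

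| Section | Follow-up after two exacerbated sessions | Handling in analysis |
|---|---|---|
| 7.0 | Stay in the study, visits to Day 90 | Out of the group analysis; looked at as a subset |
| 9.2 | Removed from the study; clinic follow-up | Not stated |
| 10.0 | Participation ended, scope unclear | Not stated |
| 14.1 | Described as removed from the study | Can be censored in the Cox model |

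The firm contradiction is between 7.0 (stay) and 9.2 (removed). No section counts these participants' clearance dates in the primary comparison.

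**Step 2. Inputs**

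From section 13.0: mean time to clearance 43 days, SD 20, 53 per group, target reduction 7 days. The protocol gives no share removed and no bias figure, so there is nothing of its own to reproduce here. The 53 is taken as given; whether it follows from the stated difference and SD is a separate matter.

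Assumed: the share q of the exercise arm removed, and the correlation ρ between the tendency to exacerbate and clearance time.

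**Step 3. Model with no true effect**

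For each participant Z ~ N(0,1), and clearance time T = F⁻¹(Φ(Z)). F is a gamma distribution with shape (43/20)² = 4.62 and scale 20²/43 = 9.30 in both arms. The tendency to exacerbate is L = ρZ + √(1−ρ²)ε, with ε ~ N(0,1). An exercise-arm participant is removed if L > Φ⁻¹(1−q), and is then either censored on a random day from 4 to 13 or excluded. Follow-up is cut at Day 90. The Cox model has arm only, with a two-sided 5% test and 4,000 runs per cell. HR above 1 means faster clearance on exercise.

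**Step 4. Results, unadjusted**

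| q | ρ | HR, censored | Type I error | HR, excluded | Type I error |
|---|---|---|---|---|---|
| none removed | – | 1.00 | 5.7% | – | – |
| 20% | 0 | 1.00 | 5.2% | 1.00 | 4.8% |
| 10% | 0.3 | 1.07 | 6.0% | 1.07 | 6.1% |
| 10% | 0.5 | 1.13 | 9.6% | 1.12 | 8.9% |
| 20% | 0.5 | 1.22 | 15.4% | 1.23 | 15.0% |
| 20% | 0.7 | 1.37 | 30.4% | 1.37 | 30.3% |

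At 20% and 0.5, nearly all false positives favour exercise: 15.1% under censoring, against a nominal 2.5% in that direction.

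Runs with lognormal times of the same mean and SD agree: HR 1.22–1.24 and type I error 15–17% at 20% and 0.5 (a shorter 600-run check gave about 18%), and HR 1.56 with type I error 51% at 30% and 0.7.

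**Step 5. Hand check in days, under exclusion**

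The mean of Z among those kept is −ρ·φ(z)/(1−q), where z = Φ⁻¹(1−q). For q = 0.20, z = 0.84 and φ(z) = 0.280, so the shift is 0.5 × 0.280/0.80 = 0.175 SD, or 0.175 × 20 = 3.5 days. The simulation gives 3.7. For q = 0.10, φ(z) = 0.1755, so 0.5 × 0.1755/0.90 × 20 = 1.95 days. The simulation gives 2.0.

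**Step 6. Effect of the planned adjustment**

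At 20% and 0.5 under censoring, assume half the correlation runs through one measured baseline covariate that is in the model. HR falls to about 1.11–1.13 and type I error to about 9–10%. If all of it ran through that covariate, HR would be 0.99.

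**The case against.** The strongest reply is that the bias is not demonstrated. Its direction and size rest on q and ρ, and the protocol gives neither. Section 7.0 speaks only of a potential subset, and the trigger needs two consecutive sessions. At ρ = 0 there is no bias, only lost information, and at 10% and 0.3 type I error is close to nominal. The planned model also adjusts for initial PCSS, an obvious common cause of exacerbation and slow clearance. All of this stands as a limit on the magnitude. It does not rescue the rule, because removal depends on a response after randomisation that baseline covariates need not capture.

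Section 14.1 is also loosely worded: it says the method can censor, not that it will. But 7.0 states removal outright, and the two handlings give almost the same result.

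Four stronger readings are tempting and are not supported:

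- **That the trial's result will be biased.** This needs exacerbators to clear later. Section 9.2 makes that plausible and does not establish it.
- **That 7.0 and 14.1 give irreconcilable analysis rules.** The group analysis in 7.0 could mean the mixed models of 14.2, with censoring kept for the Cox model. Both would still select on exacerbation in one arm.
- **That the artefact could match the whole planned effect.** Setting HR 1.22 beside 43/36 = 1.19 suggests this, but that ratio is a hazard ratio only for exponential times, whose SD equals the mean; here it is 20 against 43. In days, the exclusion figure of 3.7 is about half the 7-day target, and it is a difference in means, not the planned Cox estimate.
- **That section 11.0 adds to the one-sided bias.** It says that on a participant's "withdrawal from the study, their data will be safely discarded with no consequences to the participant". This covers withdrawal in either arm. It sits badly with censoring for attrition, since discarded data cannot contribute time at risk. Attrition may, however, also mean loss without withdrawal, so the conflict is partial and secondary.

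**Conclusion.** The concern holds in conditional form. It is certain that the exacerbation rule exists only in the exercise arm, that it acts after randomisation, that the protocol foresees excluding or censoring on it, and that 7.0, 9.2 and 10.0 do not agree on follow-up. Attrition, named in the same sentence of 14.1, can occur in both arms and is not part of the one-sided problem.

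Given that exacerbators tend to clear later, the bias favours exercise. Without covariates it runs from nothing at correlation 0, through HR about 1.06–1.07 (type I error 6–7%) at 10% and 0.3 and about 1.22 (15–18%) at 20% and 0.5, to about 1.56 (51%) at 30% and 0.7. The unadjusted figures lean high for the planned model. Confidence is high on the structure and the contradiction, and low on the magnitude.

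Because a primary endpoint is affected and the remedy is cheap, this should be corrected before analysis.

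**What to change.** In sections 7.0, 9.2, 10.0 and 14.1, state one rule:

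- All randomised participants are analysed in the arm assigned.
- Stopping the exercise sessions is not a reason for exclusion or censoring.
- Time runs to the clearance date in the medical record, with censoring only at true loss to follow-up or at a stated end of follow-up. Day 90, the participant duration in the protocol summary, is one option; no section currently states it as the cut-off for clearance.
- The exacerbation subset is reported descriptively. Censoring or excluding it appears only as a labelled sensitivity analysis.

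Reconcile 7.0, 9.2 and 10.0 on whether these participants stay in the study. The rule for stopping exercise itself need not change for this, and no view is taken on it.

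As a secondary change, section 11.0 should keep data collected up to withdrawal unless the participant asks for deletion.

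The cost is protocol wording and probably one consent sentence on data retention. Clearance dates are already to be taken from clinic records. The price in interpretation is an estimate diluted by those who stopped exercising, but that is the effect of assigning the programme.
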